## Abstract

**Background:**

An estimated 17 million children have severe acute malnutrition (SAM) worldwide, with the majority residing in South Asia. Routine empirical antibiotics are prescribed for Community-based Management of Severe Acute Malnutrition (CSAM) to address presumed clinical/subclinical infections and improve nutritional recovery for children with uncomplicated SAM, but low prevalence of infection has been reported. Thus, targeted antibiotics (eg, single-dose azithromycin or 7-day amoxicillin) are recommended over empirical antibiotics to limit emerging antimicrobial resistance (AMR), but there is limited literature on the relevance.

**Objective:**

This study aims to (1) estimate the prevalence of clinical/subclinical infections and describe AMR patterns among children aged 6-59 months with uncomplicated SAM and assess associations with sociodemographic, clinical, and nutritional factors; (2) explore health-seeking behavior, antibiotic use, and care preferences among caregivers and health care providers; and (3) evaluate the efficacy of 7-day amoxicillin versus single-dose azithromycin versus no antibiotics in weight gain and nutritional recovery among children with SAM.

**Methods:**

This mixed methods study will be part of the ongoing CSAM program implemented in selected districts of Telangana, India. Phase 1 will be a cross-sectional analytical study with a laboratory component to estimate the prevalence of clinical/subclinical infections and AMR among 606 children. Phase 2 will use a qualitative design (focus group discussions with caregivers and in-depth interviews with health care providers) to explore perceptions and practices related to management and antibiotic use among the children. Phase 3 will be an open-label, parallel-group randomized controlled trial (RCT) with three groups of ~250 children each to compare nutritional recovery: 7 days of amoxicillin + standard nutritional care, single-dose azithromycin + standard nutritional care, and no antibiotics + standard nutritional care (control). Children will be followed for up to 6 months, with periodic anthropometric, clinical, and laboratory assessments.

**Results:**

Participant recruitment began in June 2026. Baseline assessments, interventions, and final evaluations are anticipated to be completed over a 24-month period (ie, by May 2028). Funding was received in August 2025; ethical approval was obtained on February 17, 2025; Clinical Trial Registry – India approval was obtained on March 18, 2025; and administrative approvals from the state government are in process. Preparatory phase activities (ie, obtaining ethical approval, Standard Operating Procedure development, project team recruitment, field site identification, and meeting with district stakeholders and the state government) were completed by March 2026. As there was a delay in initiation of the RCT component of the study, phases 1 and 2 have been initiated after obtaining required approvals at this time.

**Conclusions:**

This study will provide critical evidence on the burden of clinical/subclinical infections and AMR among children aged 6-59 months with uncomplicated SAM and inform the rational use of empirical antibiotics for CSAM amid growing AMR concerns.

**Trial Registration:**

Clinical Trials Registry India CTRI/2025/03/082358; https://ctri.nic.in/Clinicaltrials/pmaindet2.php?EncHid=MTIyMDI2&Enc=&userName=

## Introduction

### Background

Acute malnutrition is defined as a condition characterized by a severe nutrient deficit due to inadequate intake of food or the inability of the body to properly absorb essential nutrients [1]. Worldwide, 45.4 million children aged <5 years have wasting [2]. In India, the National Family Health Survey (NFHS)-5 reported a 19.3% burden of wasting and a 7.7% burden of severe wasting [3]. Although the burden of wasting remains almost constant, there is an increase in severe wasting compared to NFHS-4 and NFHS-3 [3-5]. Severe wasting indicates severe acute malnutrition (SAM) and is defined as a weight-for-height z-score (WHZ) of <−3 SD, a mid-upper arm circumference (MUAC) of <115 mm, or bilateral pitting pedal edema [6].

From the management perspective, SAM is further classified into complicated and uncomplicated SAM. Children with complicated SAM exhibit no appetite or have medical complications, while those with uncomplicated SAM have a successful standard appetite test and no fever, clinical infections, or complications [7]. Children with both complicated and uncomplicated SAM have a higher risk for acute infections, such as pneumonia, diarrhea, and sepsis, which triples the mortality risk: a few reported reasons are a weakened immune system, altered gut microbiota, poverty, food insecurity, and inadequate access to health care [8,9]. The fatality rate among children with SAM receiving inpatient care ranges from 3.4% to 35%. These data show that 3.5 million deaths are estimated among children in India aged <5 years [10].

In 2013, the World Health Organization (WHO) recommended inpatient management at nutritional rehabilitation centers using medications in line with the complications exhibited for children with complicated SAM and ambulatory Community-based Management of Severe Acute Malnutrition (CSAM) using energy-dense food and empirical antibiotics for children with uncomplicated SAM [11]. The empirical administration of broad-spectrum antibiotics, such as amoxicillin, as part of Community-based Management of Acute Malnutrition (CMAM) for children with uncomplicated SAM was a strong recommendation but with low certainty of evidence as per the 2013 guidelines [11]. However, there is a lack of high-quality evidence on the efficacy of empirical antibiotic therapy for 5-7 days among children with uncomplicated SAM at the community level. In settings with low infection rates among children with uncomplicated SAM, empirical management might lead to antibiotic overuse. Even in children aged <5 years with infection, empirical antibiotics might be ineffective due to poor compliance with medications and alarming levels of antibiotic resistance [12,13]. Furthermore, the overuse of empirical antibiotics among children with uncomplicated SAM can contribute to emerging antimicrobial resistance (AMR) in the community, especially among children [13]. AMR impairs the child’s development and second-line antimicrobials can contribute to lifelong disability, and worldwide estimates for 2019 indicate that 254,000 deaths of children are attributable to AMR [14]. The irrational prescribing of antibiotics and the suboptimal use of antimicrobials are the major contributors for AMR emergence [15-17]. Thus, further evidence on the relevance and appropriateness of empirical antibiotics for CSAM among children with uncomplicated SAM is required in the wake of increasing AMR.

### Rationale of the Study

In 2023, the Government of India released the National Protocol for Management of Malnutrition in Children to strengthen the ongoing efforts and commitment to address the challenges of malnutrition [18]. Mission Saksham Anganwadi and Poshan 2.0 was launched to drive the efforts to reduce malnutrition by identifying and managing children aged <5 years with SAM in India [19]. Under this program, peripheral health workers and *Anganwadi* (rural child care center in India) teachers are trained to make initial decisions on the level of inpatient or community-based care, nutrition management, and follow-up care for the identified children aged <5 years with SAM. These children are enrolled for CSAM at *Anganwadi*s and administered empirical amoxicillin for 5 days, twice a day, along with nutritional support for 4 months [20].

Although empirical antibiotics are currently in use, recent studies from the Africa region and one from India have not found them effective in improving nutritional recovery [21]. The potential reason was either a low rate of infection among children with uncomplicated SAM at the time of identification or AMR emergence, making empirical antibiotics ineffective [22-24]. Thus, the context-specific relevance of empirical antibiotics needed to be tested by assessing infection rates among children with uncomplicated SAM at the time of identification and by exploring antibiograms.

In India, a few observational studies in tertiary care hospitals among children with complicated SAM have reported a high prevalence of diarrhea (36%), fever (34%), and pneumonia (43%) [25-27]. However, this evidence does not warrant the use of empirical antibiotics among children with uncomplicated SAM managed at the community level without any clinical symptoms of infection. In addition, there is a lack of evidence on the burden of clinical/subclinical infection among children with uncomplicated SAM in India, and it is important to decide whether empirical antibiotics are necessary for this patient group.

A study [28] from India among children with sepsis in tertiary care centers reported that 48.2% and 90.3% of the children developed AMR to gentamicin and penicillin G, respectively. Another study [29] among pediatric patients in urban Delhi found high rates of AMR to commonly used antibiotics, such as amoxicillin and cotrimoxazole. Although the studies have reported high AMR prevalence among children, the literature on the burden of AMR among children aged <5 years with uncomplicated SAM in India is limited. Antibiograms and AMR profiles are necessary to decide whether the current choice of amoxicillin for empirical management of children with uncomplicated SAM is relevant.

Empirical antibiotics administered for 7 days can lead to poor medication compliance and suboptimal antibiotic use. In Niger, West Africa, empirical mass administration of a single dose of azithromycin was found feasible in a programmatic setting and was effective in reducing mortality due to meningitis, dysentery, malaria, and pneumonia among children aged <5 years [30,31]. A pilot randomized controlled trial (RCT) in Burkina Faso reported similar weight gain and fewer adverse events in the single-dose azithromycin group compared with the 7-day amoxicillin group [32]. However, azithromycin has not been tested in trial mode among children with uncomplicated SAM, and an RCT among children with uncomplicated SAM would generate evidence on the effectiveness of empirical antibiotics in nutritional recovery and aid in deciding whether a single dose of azithromycin is enough.

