Rao et al [34] reported the WHZ mean (SD) as –1.29 (0.84) in the amoxicillin group and –1.45 (0.93) in the control group at the end of 2 weeks of intervention. Considering these values, with 95% CI and 80% power, we will require 480 participants in each group. Considering logistic issues, feasibility, and long follow-up, we will recruit 250 children aged 6-59 months with uncomplicated SAM per group.

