A list of children with uncomplicated SAM will be obtained from the NHTS website. The children will be visited at their homes to confirm their nutritional category. At enrollment, each child will be assigned a unique identification number based on the number in the list. After baseline assessment, children will be randomized using stratified randomization to one of three groups: amoxicillin (5 days, twice a day, 15 mg/kg based on weight band + standard nutritional care), azithromycin (single dose, 20 mg/kg + standard nutritional care), or control (no antibiotics + standard nutritional care). Children with subclinical infection will be randomized to either the amoxicillin or the azithromycin group in a 1:1 allocation ratio. Children without any subclinical infection will be randomized to the amoxicillin, azithromycin, or control group in a 1:1:2 randomization sequence to balance the stratified randomization based on subclinical infection status. The remaining children who will be assessed clinically for uncomplicated SAM, who pass the appetite test, and who are found eligible will be assigned to one of the three groups in a 1:1:1 randomization sequence; these children will be recruited after completion of the phase 1 enrollment. Around 150-200 participants are expected to be recruited after phase 1 enrollment to fulfill the sample size requirement for phase 3.

Three separate randomization sequences of unequal block sizes will be generated. A non–peer-reviewed study [40] from Bangladesh reported that 36% of children with uncomplicated SAM have elevated CRP and α1-glycoprotein. Assuming that 35% of children with uncomplicated SAM might have a subclinical infection [40], a randomization sequence will be generated using online software. The allocation will be concealed centrally in the institute. Based on the intervention plan, study participants and administrators will not be masked in the study.

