Data analysis will be performed in Stata version 18.0 software using intention-to-treat analysis at the end of the study. Per protocol analysis will also be performed as a secondary analysis at the end of the study. Interim analysis will be part of the quality parameter (at the end of the first year). The WHZ and MUAC will be expressed as mean (SD) or median (IQR) with 95% CIs based on data normality. The presence of bilateral pitting edema will be expressed as proportions with 95% CIs. Independent variables (child’s age in months and mother’s age) will be expressed as mean (SD) or median (IQR) with 95% CIs based on data normality. Factors such as education status, type of delivery, and birth complications will be expressed as proportions with 95% CIs. Outcomes such as episodes of acute illness, day care absenteeism, parenteral absenteeism, number of hospital visits, and food consumption will be expressed as mean (SD) or median (IQR) with 95% CIs based on data normality. Outcomes such as the presence of sepsis and mortality status will be expressed as proportions with 95% CIs. The chi-square test will be performed to analyze the association between outcomes and categorical independent variables. An unpaired *t* test (or Mann-Whitney *U* test) will be performed to assess the association between outcomes and continuous independent variables. Poisson regression analysis (bivariate and multivariate) will be conducted to explore the association between dependent and independent factors. Adjusted risk ratios with 95% CIs will be reported for factors included in the multivariate Poisson regression model.

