### Conclusion

The evaluation of single-dose azithromycin as an alternative therapy regimen for SAM may offer operational advantages, particularly in improving medication adherence and reducing the treatment burden in large-scale programs implemented through community platforms, such as *Anganwadi*s in India. Future research should focus on longitudinal studies to further explore the impact of antibiotic use on relapse rates, growth outcomes, and AMR patterns over time.

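### The plan asks whether single-dose azithromycin suffices, but nothing in its analysis or sample size bounds how much worse than amoxicillin azithromycin could be

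*Protocol article*

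**What the plan says.** The Rationale of the Study motivates azithromycin by the compliance problems of a 7-day course and by a pilot trial that found similar weight gain on the two antibiotics. It then says the trial will "aid in deciding whether a single dose of azithromycin is enough". The Conclusion returns to this: "The evaluation of single-dose azithromycin as an alternative therapy regimen for SAM may offer operational advantages", naming adherence and treatment burden.

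The Study Objectives give a three-way efficacy comparison of amoxicillin, azithromycin and no antibiotic, without naming a superiority, non-inferiority or equivalence hypothesis.

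Sample Size, Phase 3, uses the WHZ means and SDs of an earlier trial's amoxicillin and control groups at 2 weeks. It concludes "with 95% CI and 80% power, we will require 480 participants in each group", and then: "Considering logistic issues, feasibility, and long follow-up, we will recruit 250 children aged 6-59 months with uncomplicated SAM per group". It makes no assumption about azithromycin.

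Data Entry and Analysis, Phase 3, plans intention-to-treat analysis with per-protocol as secondary. On tests it says: "The chi-square test will be performed to analyze the association between outcomes and categorical independent variables". An unpaired t test or Mann-Whitney test is given for continuous variables, and Poisson regression for adjusted risk ratios. The 95% CIs promised for WHZ and MUAC accompany the summary statistics. None is specified for a difference between arms.

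**The concern.** Whether an easier regimen is enough is a question about how much could be lost by using it. It is answered by an upper bound on the deficit. A test of difference supplies no such bound: when it is non-significant, the deficit may be nil or may be as large as the interval allows.

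The article says its results are meant to inform national guidelines. It also cites earlier trials with no significant differences, one of them with 100 children, as part of the case against antibiotic benefit. Without a stated rule, a reader of the final report could take a non-significant azithromycin-amoxicillin comparison as support for replacing one regimen with the other.

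**Working it through.** **Inputs.** From Sample Size, Phase 3: mean WHZ –1.29 (SD 0.84) on amoxicillin and –1.45 (SD 0.93) on control at 2 weeks; 80% power; 250 per group planned. A two-sided 5% level is my reading of the 95% CI stated there. No Phase 3 dropout rate is given, so 10% and 20% are shown as assumptions. No margin is given, so the margins below only show a range.

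**The plan's own figure.**
- Difference: 1.45 – 1.29 = 0.16.
- Pooled SD: √[(0.84² + 0.93²)/2] = 0.886.
- n per group = 2 × (1.96 + 0.842)² × 0.886² / 0.16² ≈ 482, against 480 stated.

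The figure reproduces as a two-sided difference calculation (a one-sided one gives 380), and it concerns amoxicillin versus control.

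**Precision of azithromycin minus amoxicillin at 250 per arm.**
- SE = 0.886 × √(2/250) = 0.0793.
- 95% CI half-width = 1.96 × 0.0793 = 0.155 WHZ.
- A just non-significant observed deficit is about 0.155, and its interval reaches 0.155 + 0.155 = 0.31 WHZ.

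**Chance that a real deficit is non-significant.** Power = Φ(deficit/SE – 1.96).

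| True deficit (WHZ) | Analysed per arm | Power | Non-significant |
|---|---|---|---|
| 0.16 | 250 | 52% | 48% |
| 0.16 | 225 | 48% | 52% |
| 0.16 | 200 | 44% | 56% |
| 0.10 | 250 | 24% | 76% |

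**What a non-inferiority margin would require.** With one-sided 2.5%, truly equal arms and no covariate adjustment:

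| Assumed margin (WHZ) | n per arm for 80% power | Power at 250 |
|---|---|---|
| 0.10 | 1233 | 24% |
| 0.16 | 482 | 52% |
| 0.20 | 309 | 71% |
| 0.22 | 255 | 79% |
| 0.25 | 198 | 88% |

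The smallest margin with 80% power at 250 per arm is (1.96 + 0.842) × 0.0793 = 0.22 WHZ (0.23 at 225, 0.25 at 200). That exceeds the whole 0.16 amoxicillin-control difference used for sizing. Adjusting for baseline multiplies the SE by √(1 – r²). With an assumed baseline correlation r of 0.5, 0.6 or 0.7, power at a 0.16 margin is 64%, 71% or 81%.

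**Could azithromycin versus control stand in?** Only in part. Study Procedure, Phase 3, says: "Children with subclinical infection will be randomized to either the amoxicillin or the azithromycin group in a 1:1 allocation ratio". For these children, assumed there to be 35%, azithromycin versus amoxicillin is the only randomised contrast. Control is allocated only among children without subclinical infection (1:1:2) and among those recruited after phase 1 (1:1:1). Amoxicillin to azithromycin is 1:1 in all three sequences.

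**The case against.** A reader might infer that the plan intends to treat p>0.05 as equivalence, or that this is a non-inferiority trial with its margin left out. The documents support neither. No decision rule is stated for this contrast, the wording about a single dose being enough closes a background section, and the formal objectives are three-way efficacy comparisons. The Conclusion claims operational advantages, not equal efficacy. The Introduction also reports high resistance to amoxicillin and a mortality benefit of single-dose azithromycin elsewhere, so a difference in either direction is plausible and a difference test is not absurd.

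Two further points stand. First, 0.16 WHZ is not a difference the plan calls clinically relevant: it is a 2-week gap from a trial the article itself describes as showing no significant differences. Second, simply adding a margin of up to 0.16 would be a poor remedy. It would preserve none of the assumed amoxicillin effect, and the plan doubts that amoxicillin has one. The 52% power also partly restates the shortfall from 480 to 250, which the article discloses openly.

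What the objection does not remove is that the Rationale promises an answer on sufficiency, while the stated tests and sample-size basis give no bound from which to draw it.

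**Conclusion.** The concern holds as a gap between the claim and the analysis. The plan wants to learn whether azithromycin suffices, yet it commits to no between-arm interval, margin or rule for that contrast and was sized for another pair of arms. At 250 per arm the difference would be known to about ±0.155 WHZ, and a true deficit of 0.16 would go undetected in about 48% of trials. Non-significance therefore could not justify a conclusion of sufficiency. That the investigators would draw that conclusion is not shown.

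The figures rest on 2-week SDs, while the primary outcomes are at 16 weeks and 6 months. They also assume no covariate adjustment and, except where shown, no dropout, so they are indicative.

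**What to change.** 1. Report azithromycin minus amoxicillin in WHZ at 16 weeks with a two-sided 95% CI, from a model adjusted for baseline WHZ and randomisation stratum, in both the intention-to-treat and per-protocol sets. Do likewise for the other primary outcomes, each adjusted for its own baseline value.
2. State that sufficiency or similarity will not be concluded from p>0.05.
3. Choose one of two routes before outcome data are seen. Either prespecify and justify a non-inferiority margin and state its true power (about 52% unadjusted at 0.16; 80% needs about 0.22), or limit this contrast to estimation and soften the sentence in the Rationale of the Study.
4. Interpret the contrast alongside each antibiotic versus control in the strata where control is allocated, because amoxicillin's own benefit is in question.
5. Reconcile the comparator first. Amoxicillin is given for 7 days in the Abstract and Study Objectives, but for 5 days in the aim closing Need for a Control Group With No Antibiotics, in Study Procedure (Phase 3) and in Intervention Phase. The contrast cannot be defined until these agree.

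The cost is protocol wording and one model, using baseline values and strata already recorded. Estimation needs no more children; a margin tighter than about 0.22 would need more, or a real gain from adjustment, to reach 80% power. The downside is that the azithromycin question may end as inconclusive. The article reports that the randomised component has been delayed, so there appears to be time to make the change.

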### Need for a Control Group With No Antibiotics

WHO recommends one course of amoxicillin for children with uncomplicated SAM; however, this is a conditional recommendation in both the 2013 and 2023 WHO guidelines on CSAM because of the low certainty of evidence [11,33]. The 2013 guideline was largely based on a single RCT [21] conducted in Malawi (2009-2011), which reported lower mortality in the amoxicillin group (4.63%) compared with the placebo group (7.48%). The trial included 924 children receiving amoxicillin, 923 receiving cefdinir, and 920 receiving a placebo. However, around 30% of the children had HIV, with no separate outcome analysis for HIV and non-HIV groups. Nearly 70% had kwashiorkor with edema, while only 20% had marasmus (WHZ<−3 SD). The study [21] was conducted in a high-infection setting, with 82% of children reporting fever, cough, or diarrhea prior to baseline, limiting the generalizability of its findings to settings with a lower infection burden.

However, a few other studies have reported different results. A double-blinded RCT [22] conducted by the Médecins Sans Frontières (MSF) in Niger (2012-2013) among children with uncomplicated SAM (n=1199 in the amoxicillin group and n=1200 in the placebo group) reported no difference in nutritional recovery between groups. Amoxicillin reduced early inpatient admissions within 2 weeks (14%), mainly by lowering diarrhea risk, slightly shortening the recovery time (28 vs 30 days, *P*<.001), and reducing mortality among children aged >2 years. However, by 8 weeks, there were no differences in death, default, or nonresponse between groups. Amoxicillin showed no benefit among children with confirmed bacterial infections, fever, or respiratory illness, and no differences were observed in inpatient admissions or recovery among hospitalized children. Hence, the authors concluded that amoxicillin does not play a significant role in nutritional recovery and that, as the study was conducted in a low-infection setting (10% bacterial gastroenteritis, 4% bacteremia, and 3% bacteriuria confirmed by blood, stool, and urine cultures), antibiotics can be recommended in context-specific settings with high rates of infection.

An RCT [34] conducted in Kanpur, India, among 100 children with uncomplicated SAM (amoxicillin vs placebo) reported no significant differences in clinical or anthropometric parameters between groups. A systematic review and meta-analysis [24] similarly reported that the evidence on empirical antibiotic usage among children with uncomplicated SAM is weak and may require urgent testing.

The Indian Council of Medical Research’s (ICMR) 2019 “Treatment Guidelines for Antimicrobial Use in Common Syndromes” recommend empirical antibiotic use in common illnesses, such as severe sepsis and septic shock, acute bacterial meningitis, community-acquired pneumonia, and necrotizing fasciitis, only when proven to be beneficial. The guidelines also suggest de-escalating or modifying therapy based on culture and drug susceptibility [35]. There is evidence of acute respiratory infection (ARI; 50%) [36] and diarrhea from the NFHS-5 (7.3%), ARI from the NFHS-5 (2.8%), and fever or ARI from the NFHS-5 (69%) [3]. However, there is no evidence in community-based studies of confirmed bacterial infection among children, and most infections among children aged <5 years are suspected to be of viral origin. A 2004 Lancet review [37] reported that the coverage offered by the aminopenicillins group of antibiotics is only 37% in the case of pediatric sepsis in Southeast Asia and the Pacific region [37].

Considering all this evidence, the rationale behind using empirical antibiotics requires urgent assessment, and there is a dire need for a control arm without antibiotics to assess the efficacy of empirical antibiotics in children with uncomplicated SAM. Therefore, this study aims to (1) estimate the clinical/subclinical infection and AMR patterns among children with uncomplicated SAM; (2) explore health-seeking behavior, antibiotic use, and care preferences among caregivers of pediatric patients and identify challenges and facilitators faced by health care providers in patient management; and (3) compare the effectiveness of single-dose azithromycin, 5-day amoxicillin, and no antibiotic therapy on nutritional recovery and clinical outcomes.

